# ABSTRACT

**Background:** Oral health and the inability to manage this independently is a known predictor of aspiration pneumonia in vulnerable populations such as the elderly and chronically ill, with the link between poor oral health with systemic disease, morbidity and mortality demonstrated extensively throughout allied health, nursing, and dental literature. If oral health is reduced, people are not only at greater risk of aspiration pneumonia, but they may have pain or poorer dentition which impacts on mastication and swallowing, and reduced oral intake, with potential for malnutrition, poorer health outcomes and reduced quality of life.

There are currently limited oral care protocols with measurable outcomes that are used in hospitals and care facilities in Australia. This is of concern to speech pathologists due to the link between poor oral care and the potential for aspiration in vulnerable populations such as the elderly. However, a recent literature review by [name] and colleagues (2021) reported improvements in oral hygiene, oral behaviours and swallowing, along with breathing and speech have been found to be associated with the use of myofunctional devices.

**Methods/Design:** This project is a feasibility study for a new five-week intervention for oral hygiene and dysphagia for residents 65> years old in an aged care setting. Feasibility will be measured through the acceptability of the treatment and measured by number of consenting participants, trial completion rates, treatment adherence, and staff implementation. Efficacy will be determined by secondary outcome measures through pre and post assessment of oral health, perceived dysphagia symptoms and presence of dysphagia.

**Discussion:** The results of this trial will provide important information regarding the acceptability and feasibility of a myofunctional device in improving oral care and dysphagia in elderly patients in an aged care facility. This knowledge will further guide, and inform design of a larger trial or future research.

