# AIM OF STUDY / RESEARCH QUESTION

The objective of this study is to assess the feasibility and efficacy of a using a myofunctional device to improve oral care and swallowing function in an aged care population.

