# STUDY DESIGN/METHODOLOGY

The protocol presented is based on both the Standard Protocol Items: Recommendations For Interventional Trials (SPIRIT) (2013) and Consolidated Standards of Reporting Trials (CONSORT) (2018) guidelines, to conduct an acceptability and feasibility pilot study. The proposed protocol is for a new intervention. There have been no previous trials using the MyoMunchee
[figure not shown]
 (a myofunctional device) in the area of oral hygiene and dysphagia with those in an aged care setting. A cluster randomised control trial in Sweden by Hagglund and colleagues (2019) utilised a myofunctional device (used for promoting lip closure and nasal breathing) for oral neuromuscular training for those 65 years and older in short term care units with impaired swallowing. Hagglund and colleagues (2019) study indicated that swallowing function significantly improved for those in the intervention group immediately following 5 weeks of therapy with the use of the myofunctional device, and a significant reduction in signs of aspiration compared to the control group 6 months post treatment.

The use of this study will provide important information regarding the feasibility and efficacy of a new treatment for oral hygiene and dysphagia with the MyoMunchee
[figure not shown]
, and provide information for calculating the sample size needed for a randomised control trial (In, 2017, & Eldridge, et al., 2016). Thabane and Lancaster (2019), In (2017), and Eldridge, et al., (2016) highlight the importance of feasibility studies to further guide and inform conduct and design of a larger clinical trial or future research.

The feasibility of the treatment intervention will be measured by way of:

- Verbal survey of the residents receiving the intervention regarding experience using the device, using a 5-point Likert scale (very difficult – very easy), and dichotomous questions (yes – no) (Appendix A).
- Questionnaire for care staff (nursing/allied health) in the implementation and acceptability of assisting participants with the myofunctional device, using both a 5-point Likert scale (very difficult – very easy), dichotomous questions (yes – no), and free text (Appendix B).
- The consenting rates,
- Treatment completion rates,
- Treatment adherence (which will be monitored on the daily check list provided by care staff, see Appendix C, D, E, F, G).

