Efficacy will be measured through the collection of pre and post intervention outcome measures using validated instruments to measure perceived dysphagia symptoms, and the presence of dysphagia. These outcome measures include:

- Oral Health Assessment Tool (OHAT) (Chalmers, Johnson, Tang, Titler, 2004) (Appendix H)
- Timed Water Swallowing Test (TWST) (Hughes &Wiles, 1996) (Appendix I)
- Test of Mastication and Swallowing Solids (TOMASS) (Huckabee, et al., 2018) (Appendix J)
- Mann Assessment of Swallowing Ability (MASA) (Mann, 2002) (Appendix K)
- Eating Assessment Tool (EAT-10) (Belafsky, et al., 2008) (Appendix L)
- Mini Mental State Examination (MMSE) (Malloy & Clarnette, 1999) (Appendix M)
- Functional Oral Intake Scale (FOIS) (Cary, Mann, & Groher, 2005) (Appendix N)

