# STUDY OUTCOMES

1. **Quantitative**
2. **Primary Outcome**

Feasibility and acceptability of treatment intervention. This will include the number of participants approached versus consented, completed treatment rates, and adherence to the intervention (monitored by care staff with supervision of the intervention, and completion of daily intervention sheets).

1. **Secondary Outcome(s)**

Secondary outcome measures will be collected both pre and post intervention, and are outlined in Table 1.

**Table 1** Secondary outcome measures for collection pre and post intervention

| Outcome Measure | Reference | Outcome | Description |
| --- | --- | --- | --- |
| Oral Health Assessment Tool (OHAT) | [6] | Oral health | Reliable and valid screening tool for use in aged care and with cognitive impairment; Approximately 7-8 minutes to administer; 8 items, Rating scale – 0 = healthy, 1 = changes, 2 = unhealthy; Total score out of 16, The higher the score the worse the oral health; Items that score 1 indicate intervention is required, and items scoring 2 indicate referral to a dental professional is required |
| Timed Water Swallow Test (WST) | [18] | Aspiration risk | Swallow speed is a sensitive indicator for identifying patients at risk of swallow dysfunction; Choking in 100ml WST may be a potential indicator for follow up aspiration; Measures swallow time, number of swallows and observes for signs of choking; Abnormal swallow is defined as a speed below 10ml/s (amount of water divided by elapsed time); Count the number of swallows taken to consume 100mls water; Time taken to consume 100mls water |
| Test of Mastication and Swallowing Solids (TOMASS) | [17] | Mastication ability | Quantitative assessment of solid bolus ingestion; Sensitive in detecting changes in performance ability of mastication; High interrater and test-retest reliability; Count number of bites, number of masticatory cycles per bite, number of swallows per bite; More likely to identify patients with subtle oral phase impairment or bolus transition issues; Normative ranges in older adults: number of bites (male 1.47/female 1.87), time in seconds (male 32.61/female 41.85), total number of swallows (male 3.61/female 3.5), masticatory cycle (male 37.6/female 41.65) |

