# STUDY PROCEDURES

1. **Recruitment of participants**

All residents and care staff who meet the selection criteria will be eligible to participate in this study. They will be identified by the Nursing Unit Managers (NUM) and the speech pathologist/s at Maroba Aged Care and provided with an information flyer (Resident Information Flyer, Appendix O. Care Staff Information Flyer, Appendix P). The residents/families of residents/care staff will be provided with a participant information statement (Residents, Appendix Q. Care staff, Appendix R) regarding the study, and then followed up by the NUM/speech pathologist for interest in study participation. There will be an opportunity for residents, family of residents, and care staff to ask questions before and after consenting to participation. Questions regarding the study can be directed by the staff at Maroba Aged care to the Principal Investigator. Residents/family of residents/care staff will be required to sign and provide written consent for participation (Residents, Appendix S. Care staff, Appendix T). Consideration and return of consent for participation in the study will be 7 days after initial contact.

Explanation will be provided to residents/family of residents that their usual oral health care and dysphagia treatment will not vary with or without participation in this study. Further to this, a statement will be provided to participants that based on the results of the pilot study, the larger clinical trial may not be performed.

This research will involve the use of information without personal identifiers and it will be obtained from individuals or gathered from medical files by care staff appointed by Maroba Aged Care. The existing data information seen in section 9d. will be collected for each consented resident.

As this is a feasibility study utilising a myofunctional device not previously trialled in this setting, all consented residents will receive the treatment intervention to better understand acceptability of the device and feasibility of completing a larger trial. No randomisation of participants will occur. The number of participants that will be aimed for recruitment – up to 50 residents and 10 staff. This is based on the available recruitment pool, and the number of residents who may not give consent. Because this is a feasibility study this does not require sample size base.

The period of time for expected time to recruit participants is four weeks.

1. **Study procedures**

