Staff:

Education will be provided before the commencement of the trial intervention by the principal investigator from the University of Newcastle to care staff, regarding familiarization and instructions for use of the myofunctional device (MyoMunchee
[figure not shown]
), cleaning and storage of the device, and documentation of device use.

The use of a myofunctional device (MyoMunchee
[figure not shown]
) will be required for each participant for the duration of this intervention and will be provided in kind by MyoMunchee
[figure not shown]
. Further explanation regarding the cleaning, cleaning schedule and storage of this will be provided in the treatment protocol as per MyoMunchee
[figure not shown]
 cleaning protocol.

The research team will provide the residents/care staff with instructions and a guide for the use of the device. This will require active use of the device with the action of chewing.

The use of the myofunctional device will be monitored by the care staff at Maroba Aged Care, with documentation on a daily checklist provided for each participant. The daily checklist will be collected by the care staff at Maroba Aged Care at the end of each week of intervention and entered into an electronic database each week by the principal investigator.

Following the five week intervention, the care staff will be asked to complete a questionnaire regarding acceptability and feasibility of the trial intervention.

Residents:

Once participants who meet the selection criteria are enrolled in the study, outcome measures will be collected and stored by the principal investigator from the University of Newcastle. The collection of outcome measure should take approximately 60 minutes for each participant.

There will not be any alteration to the participant’s usual intervention for oral care or swallowing treatment unless this is deemed appropriate by the usual treating speech pathologist/s at Maroba Aged Care, or the treating medical/nursing team.

The trial intervention using the myofunctional device will commence within two weeks post pre-treatment outcome measure collection.

The myofunctional device (MyoMunchee
[figure not shown]

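### The protocol says pre-post change in a single treated group will determine efficacy, but without a comparator it can only describe within-resident change

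*Protocol*

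**What the plan says.** The efficacy claim appears in five places in the Protocol.

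- Abstract, Methods/Design: "Efficacy will be determined by secondary outcome measures through pre and post assessment of oral health, perceived dysphagia symptoms and presence of dysphagia".
- Aim of Study / Research Question: the objective is to "assess the feasibility and efficacy of a using a myofunctional device to improve oral care and swallowing function".
- Study Design/Methodology, before the list of instruments: "Efficacy will be measured through the collection of pre and post intervention outcome measures using validated instruments".
- Study Design/Methodology, on the purpose of the study: it is to inform on both the feasibility and the efficacy of a new treatment.
- Outcomes and Significance: feasibility and efficacy results will guide the design of a randomised trial.

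The design is stated under Study Procedures, Recruitment of participants. All consented residents, up to 50, receive the device, and "No randomisation of participants will occur". Data Analysis specifies a paired t-test for pre-post comparisons, an effect size with 95% confidence interval, and significance at p<0.05. It adds a linear regression adjusting for age, cognition, adherence, comorbidities and independence in using the device.

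On the later trial, Background and Significance says the study will help determine its sample size. Study Design/Methodology says more cautiously that it will "provide information for calculating the sample size needed for a randomised control trial".

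**The concern.** Efficacy means change caused by the device. That requires an estimate of what would have happened to the same residents over the same weeks without it, and this study has no source for one. Several other causes of change are present in the protocol or inherent in pre-post measurement:

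- **Time and repeat testing.** The same tests are given twice to the same people, with a five-week intervention between them.
- **Usual care.** Oral care and swallowing treatment are to stay as they are "unless this is deemed appropriate by the usual treating speech pathologist/s at Maroba Aged Care" or by the medical or nursing team, so they may change between assessments.
- **Unblinded rating.** The principal investigator collects the outcomes, and every resident is treated. A second clinician checks reliability in only 10% of residents.

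If the wording stays, a significant paired test would be reported as efficacy, as the protocol directs, and carried into the planning of the randomised trial.

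**Working it through.** The protocol gives no power, standard deviation, correlation or expected change, so it has no figure to reproduce. The check has three steps.

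**1. What the planned analyses can identify.** Write a resident's mean change as device effect plus background change. The paired t-test estimates the sum. The regression adjusts that change for resident characteristics and adherence. It cannot remove a background change shared by all residents, because nobody is observed without the device. Adherence is not randomised, so comparing residents who used the device more with those who used it less does not replace a control group.

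**2. How often background change alone would look like efficacy.**

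Inputs:
- n = 50, the stated maximum.
- Significance level 0.05 as stated. Two-sided testing is assumed, as sidedness is not given.
- Device effect zero (assumed).
- Background improvement s = 0.2 of the outcome SD (assumed).
- Pre-post correlation r = 0.5, 0.8 or 0.9 (assumed), with equal SDs before and after.

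The SD of the change is SD × √(2(1−r)), so the standardised change is d_z = s/√(2(1−r)). The t statistic has noncentrality d_z√n with 49 degrees of freedom and critical value 2.010.

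| r | d_z | d_z√50 | Significant improvement |
|---|---|---|---|
| 0.5 | 0.2/1.000 = 0.200 | 1.414 | 28% |
| 0.8 | 0.2/0.632 = 0.316 | 2.236 | 59% |
| 0.9 | 0.2/0.447 = 0.447 | 3.162 | 87% |

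With no background change, the rate in the improvement direction is 2.5%. At r = 0.8, a shift of 0.1 SD gives 19% and one of 0.3 SD gives 91%. With an assumed 35 completers and r = 0.8, shifts of 0.1, 0.2 and 0.3 SD give 15%, 44% and 78%.

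**3. What one arm can give the later trial.** It can estimate the outcome SD, the pre-post correlation, and the consent, completion and adherence rates. At n = 50 the 95% confidence limits for an SD are √(49/70.22) = 0.835 and √(49/31.55) = 1.246 times the estimate. Required sample size scales with the SD squared, so it is known to within a factor of about 0.70 to 1.55.

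One arm cannot estimate the between-arm difference. To illustrate, suppose a pre-post change of 0.5 SD were used as that difference. The number per arm, 2(1.96 + 0.8416)²/d², is 63 for 80% power. If 0.2 SD of the change was background, the true difference is 0.3 SD and 175 per arm are needed. Power with 63 per arm is then Φ(0.3 × √31.5 − 1.96) = 39%. The protocol does not say that it will take this step. The figures show only why it should be ruled out.

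**The case against.** The strongest reply is that this is a feasibility study. Study Outcomes makes feasibility and acceptability primary, to be reported as numbers and percentages. The abstract's discussion speaks of acceptability and feasibility. The single-arm design is stated openly and justified for that purpose, and no progression rule depends on a p-value. All of this stands. It limits the seriousness of the point and means that no redesign is needed. It does not remove the efficacy wording, which is current text in five places, one of them the objective.

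Three stronger readings are tempting, and the documents do not support them.

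- **That the study can contribute nothing to the sample size of the randomised trial.** It can supply the quantities in step 3. The design section promises only information, and no section says that the pre-post effect size will be the target difference. The wording in Background and Significance leaves that use open but does not plan it.
- **That the baseline oral health assessment itself triggers treatment.** Table 1 notes that "items scoring 2 indicate referral to a dental professional is required", but this describes the instrument. No study procedure sends the result to the facility or arranges a referral.
- **That residents whose diet changed should be left out of the Functional Oral Intake Scale (FOIS) analysis.** The scale measures oral intake, so a diet upgrade may be the benefit itself. Excluding those residents would condition on a post-treatment outcome.

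A further fair objection is that the percentages depend heavily on the assumed correlation. They do, which is why a range is shown.

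**Conclusion.** The point holds for the efficacy claim. As designed, the study can describe how residents change over the intervention period; it cannot attribute that change to the device, and neither planned analysis alters this. That conclusion follows from the absence of a comparator and needs no numerical assumption. The 28% to 87% range rests on an assumed 0.2 SD background shift, correlations of 0.5 to 0.9, no device effect and 50 residents with both assessments. It illustrates the size of the problem and does not predict it.

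On the later trial's sample size, the point is narrower: the protocol should say which quantities will be carried forward. The severity is should-fix. The primary feasibility outcome is unaffected.

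**What to change.** 1. In the Abstract, Aim of Study, Study Design/Methodology (both places) and Outcomes and Significance, replace efficacy with preliminary (exploratory) within-resident change.
2. In Data Analysis, label the pre-post tests and effect sizes as exploratory, keep the 95% confidence intervals already planned, and state that no efficacy conclusion will be drawn.
3. In Background and Significance and Study Design/Methodology, state that the study will supply the outcome SD, the pre-post correlation, and the consent, completion and adherence rates for the randomised trial's sample size. State also that the pre-post effect size will not be used as the between-arm target difference.
4. Optionally, record changes in oral care, dental care or diet between the two assessments and describe them alongside the results. Keep all residents in the FOIS analysis.

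The cost is protocol wording and, if item 4 is adopted, an extra field on the weekly sheets. The downside is a more modest stated claim. No change to design, sample size or outcomes is needed.

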# KEY WORDS

Myofunctional Device, Dysphagia, Oral Hygiene

# BACKGROUND AND SIGNIFICANCE

The link between poor oral health with systemic disease, morbidity and mortality has been demonstrated extensively throughout allied health, nursing, and dental literature (Danckert, Ryan, Plummer & Williams, 2016; Murray & Scholton, 2017; Ajwani, Jayanti, Burkolter, Anderson, Bhole, Itaoui & George, 2017; Wang, Huang, Chou & Yu, 2015).

Oral health is important in both children and adults. Poor oral health, such as tooth decay, gum disease and tooth loss, contributed to 4.5% of non-fatal diseases in Australia in 2015, with 78% of oral disorders in people aged 85 years and over (Council of Australian Government Health Council (COAG) 2019). Oral health deteriorates over a person’s lifetime, with children aged 5-10 years of age on average having 1.5 decayed, missing or filled teeth. In contrast, an adult 75+ years on average has 24.4 decayed, missing or filled teeth (Australian Institute of Health and Welfare (AIHW) 2021). The rate of tooth decay has been reported to be higher in the Indigenous population and those in rural and remote areas in Australia (Australian Health Ministers Advisory Council (AHMAC), 2017). Early stage gum disease, known as gingivitis, is caused by an accumulation of plaque on the teeth and gum line. It can cause inflammation and irritation to the gums which if left untreated leads to more serious periodontal disease, including damage to the soft tissue and loss of teeth (Bourke, n.d). In 2017-2018, the proportion of adults with advanced stage gum disease, periodontitis, increased with age from 51% in those 55-74 years, to 69% in those 75 years and over (COAG, 2019). Further to this, the AIHW (2021) reported that between 2017-2018 there were approximately 72,000 hospitalisations for dental conditions that may have been prevented with earlier treatment.

Factors that influence poor oral health are consumption of sugar, alcohol and tobacco; reduced access to dental services; and reduction in good oral hygiene (AIHW, 2021). The AHMAC identified four population groups that are at greater risk of poor oral health, including socially disadvantaged or low income; Aboriginal and Torres Strait Islander Australians; Those living in rural and remote areas; and people with additional and or specialized health care needs such as those with mental illness or the frail older population.

Reduced oral health and an inability to manage oral heath independently is a predictor of aspiration pneumonia in vulnerable populations such as the elderly and chronically ill (Langmore, Terpenning, Schork, Chen, Murray, Lopatin & Loesche, 1998). If oral health is reduced, not only are people at greater risk of aspiration pneumonia, they may have pain or poorer dentition. This impacts on mastication and swallowing, with potential for malnutrition, poorer health outcomes and reduced quality of life (Luong, Drysdale, Campbell, deClifford, Lam, Coutsouvelis, Danckert, 2018). Reduced oral health is associated with a number of chronic diseases including stroke and cardiovascular disease (Slade, Spencer, Roberts-Thompson, 2007).

There are several factors that impact in oral hygiene and swallowing ability. An oral breathing pattern may result in a dry oral cavity and reduced oral hygiene, which further impacts on swallowing and may increase the risk of aspiration pneumonia (Jayanti, 2006). Reduced oral hygiene may lead to pain, increased difficulties with mastication, further leading to decreased muscle bulk and poor tolerance of diet consistency (Jayanti, 2006). The need for change of diet consistency may be influenced by the risk of aspiration or choking, and in populations such as the elderly these diet changes may lead to increased risk of malnutrition, dehydration and reduction of quality of life (Hagglund et al., 2019). A study by Jayanti (2006) explored the impact of myofunctional devices on speech, swallowing and quality of life in the elderly. They reported a reduction in lip tone in the elderly population may further influence an oral breathing pattern over nasal breathing. In their scoping review of integrated oral care for stroke patients, Ajwani and colleagues (2017) reported an overwhelming lack of knowledge in oral healthcare by nursing staff in Australia. Their scoping review of the literature highlighted the importance of oral health post stroke in reducing risk of aspiration pneumonia, the need for integrated oral health programs, and also discussed the need for maintaining optimal oral health due to the links between gingivitis and cerebrovascular infarction as well as periodontal disease and stroke.

Currently there are limited oral care protocols with measurable outcomes that are used in hospitals and care facilities in Australia (Drapal, 2015). These protocols have been described as being ad-hoc and often not prioritised in patient care (Drapal, 2015). This is of concern to speech pathologists due to the impact of poor oral health on mastication, swallowing function and increased risk of aspiration. However, a recent literature review ([name], Hewat, Vertigan & Webb, 2021) found that improvements in oral hygiene, oral behaviours and swallowing, along with breathing and speech have been found to be associated with the use of orofacial myofunctional therapy and myofunctional devices (Korbmacher, Schwan, Berndsen, Bull, & Kahl-Nieke, 2004).

Orofacial myofunctional therapy is the treatment of the muscles of the face and mouth with the purpose of correcting orofacial functions (Farrell & Darcy, 2018). Orofacial myofunctional therapy has been utilized since the 1900’s to assist with orofacial dysfunction including, mandibular growth, malfunctions of the tongue, abnormal swallowing, nasal breathing and facial appearance (Farrell et al., 2018). This treatment aims to improve orofacial functions such as lip seal, mastication, swallowing, nasal breathing and oral behaviours (Wishney, Darendeliler, & Dalci, 2019). Similarly, myofunctional devices have been utilized for decades in orthodontic treatment of orofacial dysfunction (Wishney, et al., 2019). Historically, the literature regarding myofunctional devices has predominantly been in the areas of malocclusion and obstructive sleep apnoea, (Wishney et al, 2019, and Huang, Chuang, Hervy-Auboiron, Paiva, Lin, Guilleminault, 2018) but has also shown positive outcomes in sleep disordered breathing (Moeller, Paskay, Gelb, 2014 and Huang et al, 2018) and cranio-facial muscle competence (Bourke, n.d.).

The past 30 years have seen an increase in orthodontic/dental, respiratory and sleep medicine, and otolaryngology literature supporting the use of orofacial myofunctional therapy, and more specifically prefabricated myofunctional devices in the treatment of orofacial dysfunction. In a study by [name] and colleagues (pending publication) into speech pathologists’ use and outcomes of myofunctional devices in therapy programs, there was found to be both similarities and differences in the use of myofunctional devices, and the therapy programs in which these devices are incorporated. This varied across intervention areas, caseloads and diagnoses amongst speech pathologists who utilized them. [name] and Colleagues (awaiting publication) reported the type of myofunctional device, timing of introduction, utilisation in isolation, adherence, and dosage variation of myofunctional devices used contributed to successful outcomes for swallowing, oral hygiene, breathing and speech. However further education and research into myofunctional device use and guidelines to further direct their use in speech pathology intervention was recommended, along with a coordinated approach and team input in assessment and intervention.

Despite this increase of evidence, there continues to be limited research that exists in speech pathology that addresses the use and outcomes of myofunctional devices in clinical practice ([name] and colleagues, 2021). The potential impact of improvement on orofacial function, including oral hygiene and swallowing, has already been identified with the use of myofunctional devices in literature from various health disciplines (Hägglund, Hägg, Wester, & Levring Jäghagen, 2019). Along with the link between reduced oral hygiene and aspiration pneumonia (Huang, Chiou, & Liu, 2017), and the impact of a reduction in oral hygiene on quality of life (Manabe, Teramoto, Tamiya, Okochi, & Hizawa, 2015). It would be relevant to further explore treatment dosage, utilisation and outcomes of a myofunctional device in a population such as the elderly who make up a large proportion of those whose oral health and swallowing function may be impacted on (Santoro, eSivla, Cardoso, Dias, & Beresford, 2011).

Further information is needed by way of a study to analyse feasibility prior to performing a randomised control trial, by testing procedures of myofunctional device use for acceptability, recruitment and retention of participants, and further determine sample size for a larger clinical trial to evaluate the use and outcomes of a myofunctional device in oral care and dysphagia treatment in an adult population in care facilities.

